## Trial design {8}

This study is an open-label, noninferiority, two-armed, prospective, multicenter, real world trial conducted at Northwest University in Xi’an, China. The participants will be recruited from 78 hospitals across mainland China. Eligible participants will be assigned to the butylphthalide group or the control group according to their own wills. Every researcher at each study center is scheduled to recruit patients from December 2020 to June 2023. The flow chart of the trial is shown in Fig. 1.

**Fig. 1 Fig1:**
[figure not shown]
The flow chart of the trial. *: According to formula: “medication complianece = actual number of tablets / nunmber of tablets to be taken × 100%”, we calculate the patient's drug compliance. 80% to 120% will be considered as good compliance, while < 80% or > 120% will be considered poor compliance

## Methods: participants, interventions and outcomes

### Study setting {9}

We will recruit 8000 subjects from the following 78 hospitals. The list of recruitment hospitals can be found in supplementary material 1. All subjects in each treatment arm of the study will participate voluntarily after informed consent is obtained. Follow-up will be arranged at months 1, 3, 6, 12 after discharge. The project team leader communicates with the researchers of each center on a regular basis and conducts study visits in all research centers.

### Eligibility criteria {10}

#### Subject recruitment/screening

Cases will be recruited from the neurology department of 78 hospitals in China, which have a high level of diagnosis and treatment and are capable of performing CT, MRI, and other examinations. The doctor in charge of each trial center is responsible for the enrollment and follow-up of patients. Before enrollment, patients can be included only with informed consent. The follow-up is expected to be one year, and each follow-up is used to confirm whether the patient meets the exclusion criteria or not.

To ensure the accuracy of the diagnosis and treatment of stroke, the recruitment criteria for clinicians are as follows:Neurology residents in 78 hospitals;Complete at least 5 years of clinical medicine professional study and 3 years of standardized training for resident physicians;Complete the one-hour training course for this study. One-hour training includes:The basic introduction of this research protocol;The basic introduction of this research protocol;Instructions for the use of WeChat Mini Programs;Other considerations;Question and answer.

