### Exclusion criteria

Subjects will be excluded in our study if they satisfy the following criteria:Discharged, transferred to another department or died within 24 h;Severe heart, liver, kidney and other organs dysfunction or severe systemic diseases expected to survive less than one year;Can not be followed up continuously;Allergic to butylphthalide;Pregnancy, lactation or planned pregnancy;Severe mental disorders or dementia.

All patients will be recruited voluntarily and informed consent should be signed. If it is not in the patient’s interest, the patient could withdraw from the study. The reason for each withdrawal patient should be assessed and recorded in the electronic case report form (eCRF).

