## Data collection and management

### Plans for assessment and collection of outcomes {18a}

The patient’s baseline information will be collected by the research assistant while in hospital. During follow-up period, the doctor regularly makes video calls with the patient, conducts detailed consultations with the patient, collects the patient’s follow-up information and fills it in the CRF form. Afterwards, all research data will be sorted by the research assistants of each center and uploaded to the EDC platform. The data management experts of the research center conduct a unified review of the uploaded data to ensure the accuracy and completeness of the data. We will remove those centers with poor data quality, missing follow-up information, and high dropout rates from continuing to participate in the study.

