### Methods in analysis to handle protocol non-adherence and any statistical methods to handle missing data {20c}

Not applicable.

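### The exclusion criteria are checked again at every follow-up with no limit to baseline, so patients may be removed because of events that arise after treatment starts

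*Protocol article*

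**What the plan says.** Four places in the protocol article bear on this.

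- **Subject recruitment/screening.** Follow-up is expected to last one year, and "each follow-up is used to confirm whether the patient meets the exclusion criteria or not". Study setting puts the visits at months 1, 3, 6 and 12 after discharge, so all of them come after enrolment. The doctor in charge at each centre is responsible for enrolment and follow-up.
- **Exclusion criteria.** The list opens with "Subjects will be excluded in our study if they satisfy the following criteria", with no reference to a time point. It includes "Severe heart, liver, kidney and other organs dysfunction or severe systemic diseases expected to survive less than one year" and "Can not be followed up continuously;Allergic to butylphthalide;Pregnancy, lactation or planned pregnancy;Severe mental disorders or dementia".
- **Adverse events.** New cardiovascular events within one year, heart failure among them, are to be counted. Liver and kidney function, bleeding and coagulation are to be tested during follow-up.
- **Plans for assessment and collection of outcomes {18a}.** "We will remove those centers with poor data quality, missing follow-up information, and high dropout rates from continuing to participate in the study". No threshold is given, and nothing is said about the patients already enrolled there or the data already collected.

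The item on protocol non-adherence and missing data ({20c}) is answered as not applicable, so nothing there settles how a patient who leaves is treated.

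**The concern.** Exclusion criteria describe who enters a trial. Checked again after treatment has started, the same conditions are no longer baseline characteristics: they may be results of treatment, of a recurrent stroke or of dropout. A patient whose liver or heart fails during follow-up is a patient the safety comparison needs. A patient who becomes demented or unreachable after a severe second stroke is one the primary comparison needs.

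If such patients leave, each group is left with those who fared better, and the comparison holds only for them. The loss need not be equal. Concealment mechanism {16b} says that doctors know the grouping, and the doctor in charge runs follow-up, so the judgement that a criterion is met can be made with knowledge of treatment. Allergy to butylphthalide, if newly found, can arise only in someone who took it.

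**Working it through.** **1. The plan's own figure.** Inputs from Sample size {14}: 17.7% against 14.7%, two-sided 5%, 90% power. With mean rate 0.162 and pooled variance under the null:

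n = [1.960 × √(2 × 0.162 × 0.838) + 1.282 × √(0.177 × 0.823 + 0.147 × 0.853)]² / 0.030² = 3168 per group.

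This matches the protocol. Dividing by 0.85 gives 3727.1, against the stated 3727. The sample size is sound; the fault is in the design. The 15% allowance protects the number of patients and does not correct for who is lost.

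**2. Criteria set beside outcomes and harms.**

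| Exclusion criterion | What it can represent after enrolment |
|---|---|
| Severe heart dysfunction | Overlaps with heart failure, a listed cardiovascular event |
| Severe liver or kidney dysfunction | Overlaps with the liver and kidney tests listed under Adverse events |
| Expected survival under one year | Can follow a severe recurrence or a harm |
| "Can not be followed up continuously" | Is dropout itself; can follow a severe recurrence |
| "Severe mental disorders or dementia" | Can follow a severe recurrence |
| Butylphthalide allergy | A reaction to the study drug |

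Recurrent stroke is not on the list. The overlap is therefore direct for harms and cardiovascular events, and indirect for the primary outcome.

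**3. Illustration for the primary outcome.** The documents give no removal rates, so the share f of recurrences never counted in one group is an assumption. If those patients drop out of numerator and denominator, the apparent rate is 0.177 × (1 − f) / (1 − 0.177 × f):

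- f = 5%: 0.16815 / 0.99115 = 17.0%
- f = 10%: 0.1593 / 0.9823 = 16.2%

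The way leavers are handled changes little. At f = 10%, keeping them as event-free gives 0.177 × 0.9 = 15.9%. Censoring them at the uncounted recurrence gives 1 − 0.823^0.9 = 16.1%.

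If the planned effect is real and 10% of recurrences go uncounted in both groups, the rates become 16.2% and 0.1323 / 0.9853 = 13.4%. The difference is 2.8 points in place of 3.0, and power at 3168 per group is 88%. Unequal loss is thus the main worry for the primary comparison.

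**The case against.** The strongest reply is that the screening sentence speaks only of confirming whether a criterion is met. No section says what follows when one is met after enrolment; removal comes from reading that sentence with the Exclusion criteria. This is fair, and the point is put conditionally for that reason. But a check-only reading is stated nowhere, and a centre following the text as written would exclude.

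Second, events seen before a patient leaves need not be lost. The Primary outcome section has the time of recurrence recorded, Data management {19} has dropouts and adverse events recorded promptly, and the planned Kaplan–Meier, log-rank and Cox analyses would count a recurrence dated before departure. This stands. A reader might infer that the rule erases recorded safety events or recurrences, and the text does not say so. What remains exposed is whatever happens, or would have been found, after the patient leaves.

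Third, a reader might put f at 20% in the butylphthalide group and 0% among controls, get 14.7%, and conclude that the rule could produce the whole planned effect. Nothing supports that split. Even the direction is uncertain: under Explanation for the choice of comparators {6b} and Unblinding and allocation, patients with poor compliance are classed as controls, so a patient who stops early for allergy would be a control, and removal would deplete that group.

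Fourth, a reader might infer that centre removal costs material power. The text stops centres from continuing and does not say that their data are discarded. Even if six average centres were lost entirely, 8000 × 72/78 × 0.85 / 2 = 3138 per group would remain, with 89.7% power against the 90% target.

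Fifth, Who will be blinded {17a} says that researchers and research assistants are masked. That sits beside the statement that doctors know the grouping, and it does not remove the possibility of an unmasked decision.

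**Conclusion.** The concern holds as a design fault in operative text. Applied as written, the two sections select patients on post-baseline events. The safety and cardiovascular comparisons are exposed directly; the recurrence comparison is exposed indirectly, through events never ascertained after a patient leaves. Unequal removal is plausible because the doctors responsible for follow-up know the treatment, but it is not shown.

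The size and direction of the bias are unknown. The shift from 17.7% to 16.2% rests on an assumed 10% of recurrences uncounted in one group, and is an illustration, not an estimate. The conclusion also rests on meeting a criterion at follow-up leading to exclusion, which the documents imply but do not spell out. For removed centres, the defect is that the text leaves the fate of their patients and data open.

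**What to change.** In Subject recruitment/screening, replace the sentence on re-checking with a statement that the exclusion criteria are applied once, at enrolment. Add that patients who later meet one remain in follow-up and in the analysis to month 12, with the event recorded as an outcome or adverse event. Say that this concerns study participation and analysis only and leaves treatment decisions unaffected.

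In Plans for assessment and collection of outcomes {18a}, state that removing a centre stops new enrolment only, that its enrolled patients continue remote follow-up, and that its data stay in the primary analysis. Add a sensitivity analysis without those centres.

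The choice of method for patients who are still lost can be left to the analysis plan.

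The cost is a short amendment and slightly more follow-up work, since follow-up already runs remotely. The article reports that recruitment is under way, and follow-up lost through exclusion may not be recoverable, so the change should be made soon.

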### Diagnostic criteria

The diagnosis of ischemic stroke will have to meet the following criteria [28]:Acute onset. The symptoms peak in more than 10 h or 1–2 days [29];Neurologic dysfunction of any severity consistent with focal brain ischemia(such as weakness or numbness on one side of the face or body, language disorder, etc.), and few may have comprehensive neurologic dysfunction;Imaging/laboratory confirmation of an acute vascular ischemic pathology;Exclude non-vascular causes;Brain CT/MRI excluded cerebral hemorrhage.

### Inclusion criteria

Subjects will be included in our study if they satisfy the following criteria:Aged between 18 and 80 years;Hospitalized patients with ischemic stroke diagnosed by clinical symptoms or signs. The clinical manifestations are acute onset of local or diffuse brain injury. And neurological impairment conformed to the characteristics of vascular distribution;Imaging/laboratory confirmation of an acute vascular ischemic pathology;Voluntarily provide written and informed consent.

### Exclusion criteria

Subjects will be excluded in our study if they satisfy the following criteria:Discharged, transferred to another department or died within 24 h;Severe heart, liver, kidney and other organs dysfunction or severe systemic diseases expected to survive less than one year;Can not be followed up continuously;Allergic to butylphthalide;Pregnancy, lactation or planned pregnancy;Severe mental disorders or dementia.

All patients will be recruited voluntarily and informed consent should be signed. If it is not in the patient’s interest, the patient could withdraw from the study. The reason for each withdrawal patient should be assessed and recorded in the electronic case report form (eCRF).

### Who will take informed consent? {26a}

Patients diagnosed with acute ischemic stroke or their authorized agents will read the informed consent form carefully before joining the study. The researchers will interview them and help them fully understand the research content and potential risks. The informed consent form can be found in supplementary material 2.

### Additional consent provisions for collection and use of participant data and biological specimens {26b}

Not applicable.

## Interventions

### Intervention description {11a}

Butylphthalide group: 0.2 g of butylphthalide capsules three times daily plus routine treatment (aspirin 50-300 mg/d, clopidogrel 75 mg/d, etc.).Control group: routine treatment (aspirin 50-300 mg/d, clopidogrel 75 mg/d, etc.).

After discharge, all the subjects keep in touch with the doctors in charge by Wechat group or Mini Program and take medicine regularly to achieve high medication compliance. We plan to communicate with patients at a fixed time every week (for example, 8 p.m. Thursday). At that time, patients could communicate and ask any questions about the study in the WeChat group. Treatment duration is 90 consecutive days or more.

### Criteria for discontinuing or modifying allocated interventions {11b}

If patients have any discomfort, new changes in their condition, or any unexpected circumstances during the study, whether related to the study or not, they should inform their doctors in time, and doctors will make a judgment and give appropriate medical treatment.

### Strategies to improve adherence to interventions {11c}

This study is based on the network platform for follow-up by a variety of means to improve patient adherence. The doctor in charge of the patients will prescribe prescription and instruct them how to use the drug by Wechat Mini Programs. The research assistant of each research center will invite the patients to the Wechat group, remind them of the medication time, make an appointment for follow-up, and solve any questions raised by the patients in the Wechat group in time. Medication compliance will be calculated as the actual taken amount of study medication documented in a participant’s daily diary divided by the total amount planned for the participant.

### Relevant concomitant care permitted or prohibited during the trial {11d}

Medications applied to treat the underlying diseases (such as diabetes, hyperlipidemia and hypertension and others) are permitted. However, any medications used in this study should be documented in detail in case report form (CRF), including name, dose, dosage regimen, indication, and treatment period.

### Provisions for post-trial care {30}

If an adverse event occurs in a clinical trial, the committee of medical experts will determine whether it is related to therapeutic drugs. The organizer will provide treatment fees and corresponding economic compensation for the test-related damage in accordance with the provisions of “Drug Clinical trial quality Management Code of China”.

### Outcomes {12}

#### Primary outcome

##### Recurrence rate of stroke

The proportion of recurrent stroke in patients with ischemic stroke.

Recurrent stroke is defined as a new neurological deficit at least 24 h after the incident stroke according to the World Health Organization definition excluding edema, mass effect, brain shift syndrome or hemorrhagic transformation, and procedure-related strokes [30].

Our researchers will follow up patients and compare the recurrence rate of stroke between the butylphthalide group and the control group at month1, 3, 6 and 12. We will ask the patient’s condition in detail in every follow-up after discharge. If the stroke relapses, the researchers will record the time of recurrence, location of the lesion, TOAST classification, occlusive vessels, sequelae, complications, other diagnoses and related examination results. The researchers will discuss with his doctor in charge to carefully identify whether the patient has a relapse or initial progression.

#### Secondary outcome

##### NIHSS score

NIHSS score is a practical tool in the clinic to evaluate the degree of neurological impairment. NIHSS score of 42 points and 11 items, which takes into account the symptoms of anterior circulation and posterior circulation, is an objective semi-quantitative evaluation tool of stroke severity. It has been widely used in many international multicenter randomized controlled studies, and is recognized as a grading system for stroke patients’ severity with good repeatability. Generally, NIHSS score needs to be scored face to face between doctors and patients. However, due to various reasons, patients usually cannot return to the hospital for follow-up, resulting in a large number of dropouts. Therefore, in this study, Wechat is used to follow up the discharged patients. The researchers make an appointment with the patient for follow-up in advance and score the patient by video calls.

##### MRS score

The modified Rankin scale is used to measure the recovery of neurological function in patients with stroke. It has the following advantages:The operation is simple, and the score can be obtained through simple inquiry;As the effective evaluation index of functional disability level, mRS has good reliability and authenticity, and the standard mRS evaluation method is direct interview between the evaluator and the patient.MRS has no physical examination related content, so remote assessment can be realized by phone or questionnaire.

##### Adverse events

Adverse events include emerging clinical cardiovascular events within one year (sudden death/ myocardial infarction/ arrhythmia/ heart failure, etc.), and other adverse reactions of patients in the trial group. During the follow-up period, we will add tests for other adverse reactions such as liver and kidney function, bleeding and blood coagulation.

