**Methods:**

This study will be a multicenter, prospective real-world trial. We would recruit 8000 patients with ischemic stroke from 78 public hospitals in China. All participants will be allocated to one of two parallel treatment groups according to their own wills: (1) butylphthalide group: 0.2 g of butylphthalide capsules three times daily plus routine treatment (aspirin 50-300 mg/d, clopidogrel 75 mg/d, etc.); (2) control group: routine treatment (aspirin 50-300 mg/d, clopidogrel 75 mg/d, etc.). Treatment duration is 90 consecutive days or more. The primary outcome is recurrence rate of stroke within 1 month, 3 months, 6 months and 1 year in butylphthalide group and control group. The secondary outcomes included NIHSS score, the mRS score, other clinical cardiovascular events within one year (sudden death / myocardial infarction / arrhythmia / heart failure, etc.), and adverse events of patients in groups. NIHSS will be captured in the first month after discharge, and the others will be captured at the same time points as the primary end point.

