### Explanation for the choice of comparators {6b}

Doctors will make medication plans for secondary prevention according to their parents’ condition when they are discharged, and recommend (rather than forcing) them to take butylphthalide. We will manage patients through Internet means such as WeChat Mini Programs, and record their medication regularly. At the end of the whole study cycle, we will take patients who take NBP for 3 months as NBP group, and patients who refused to take butylphthalide or poor drug compliance^b^ as the control group. In addition, we will faithfully record other drugs except butylphthalide soft capsules.

*b:According to the formula: “medication compliance* = *actual number of tablets / number of tablets to be taken* × *100%”, we calculate the patient’s drug compliance. 80% to 120% will be considered as good compliance, while* < *80% or* > *120% will be considered poor compliance.*

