#### Unblinding and allocation

At the end of the study cycle, the researchers will reveal the actual medication information of the patients, taking patients with good butylphthalide compliance as the butylphthalide group, and patients without taking butylphthalide and patients with poor compliance as the control group, and compare the difference of outcomes between the two groups.

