## Statistical methods

### Statistical methods for primary and secondary outcomes {20a}

The Kaplan–Meier method is used to draw the survival analysis curve of the percentage of patients with recurrent stroke within 1 month, 3 months, 6 months and 1 year of follow-up. The LogRank method is used to compare the statistical difference in the survival curve between the two groups. The COX proportional regression model is used to calculate the risk ratio (hazards ratios) and 95% CI.

The measurement data (such as NIHSS score and modified Rankin score) is expressed by x ± s, and t-test or Wilcoxon rank sum test is used for comparison between groups. The counting data (such as clinical efficacy and adverse reactions of the two groups) is expressed by chi-square test or Fisher exact test. The subgroup analysis is carried out according to sex, age, medical history and type of stroke.Propensity score matching (PSM) is taken to ensure that the covariates are balanced and comparable. A two-sided *P* value of 0.05 or less is considered statistically significant. All the analyses are done with SPSS software 18.0 or based on R software 3.4.3.

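### The end-of-study compliance grouping counts patients who stop butylphthalide because of harm as controls, so the adverse-event comparison is biased towards no harm and can reverse

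*Protocol article*

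**What the plan says.** The grouping rule appears twice in the protocol article. Under Explanation for the choice of comparators {6b}, the control group is "patients who refused to take butylphthalide or poor drug compliance". A footnote there sets the limits: "80% to 120% will be considered as good compliance", with anything below or above that range counted as poor. Under Unblinding and allocation the timing is given ("At the end of the study cycle, the researchers will reveal the actual medication information of the patients"), and the control group is again "patients without taking butylphthalide and patients with poor compliance as the control group, and compare the difference of outcomes between the two groups".

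Adverse events are a secondary outcome. The abstract lists "adverse events of patients in groups". The Adverse events section defines the outcome as new cardiovascular events within one year plus "other adverse reactions of patients in the trial group". Statistical methods {20a} applies a chi-square or Fisher exact test to "adverse reactions of the two groups". No other grouping is described for safety, and the item on handling non-adherence {20c} is marked not applicable. Objectives {7} names safety alongside efficacy.

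**The concern.** Compliance is measured after treatment starts, and an adverse reaction can itself change it. A patient who stops early because the drug was not tolerated has low intake, and the rule makes that patient a control. The event leaves the butylphthalide numerator and enters the control numerator. The butylphthalide rate is then read largely from patients who tolerated the drug, while routine care is charged with events that butylphthalide caused. Patients who took more than 120% of the planned amount are the most heavily exposed, and they also count as controls.

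The bias runs towards no harm. With enough event-driven stopping, a drug that causes harm can look neutral or protective, on an outcome that is half of the trial's stated objective.

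**Working it through.** **Plan's own figure.** The protocol gives no adverse-event or stopping rate, so there is no safety figure to reproduce. Its sample size (3168 per group for 17.7% vs 14.7%) reproduces exactly, but it concerns recurrence and has no bearing here.

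**Inputs.** From the protocol: the 80% to 120% limits, the placing of poor compliers with controls, and the total of 8000 patients. Assumed: 4000 starters and 4000 never-takers; true event rates of 10% and 5%, so 400 events in starters (200 of them drug-caused) and 200 in never-takers; 15% poor compliance, unrelated to events, among all remaining starters.

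**Formulas.** Let s be the share of drug-caused events that push intake below 80%, and x = 200s the number of patients so moved. Expected values are:

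- Butylphthalide rate = 0.85(400 − x) / [0.85(4000 − x)] = (400 − x)/(4000 − x)
- Control rate = [200 + x + 0.15(400 − x)] / [4000 + x + 0.15(4000 − x)]

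| s | x | Butylphthalide | Control | Difference (points) |
|---|---|---|---|---|
| 0 | 0 | 400/4000 = 10.0% | 260/4600 = 5.7% | +4.3 |
| 25% | 50 | 350/3950 = 8.9% | 302.5/4642.5 = 6.5% | +2.3 |
| 50% | 100 | 300/3900 = 7.7% | 345/4685 = 7.4% | +0.3 |
| 80% | 160 | 240/3840 = 6.3% | 396/4736 = 8.4% | −2.1 |
| 100% | 200 | 200/3800 = 5.3% | 430/4770 = 9.0% | −3.8 |

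The true difference is +5.0 points throughout. The row s = 0 is stopping unrelated to events: dilution only.

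**Where the sign flips.** Both rates then equal the pooled rate, 600/8000 = 7.5%. Solving (400 − x)/(4000 − x) = 0.075 gives x = 100/0.925 = 108, so s is about 54%.

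**Milder case.** With a 3-point excess (8% vs 5%; 120 drug-caused events) and s = 25%, x = 30. The plan shows 290/3970 = 7.3% vs (200 + 30 + 43.5)/(4000 + 30 + 595.5) = 273.5/4625.5 = 5.9%. The harm is diluted but visible.

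**Second set of assumptions.** Here any patient with an event may become a poor complier, and 10% of starters without an event do. The sign flips when the following share of starters with an event become poor compliers:

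| True rates | 4000 starters, 4000 never-takers | 6000 starters, 2000 never-takers |
|---|---|---|
| 6% vs 2% | 41% | 26% |
| 10% vs 5% | 34% | 22% |

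With 4000 in each group and 6% vs 2%, stopping unrelated to events (10% for all) reduces the difference from +4.0 to +3.6 points. With no drug effect at all (5% vs 5%) and 50% of starters with an event becoming poor compliers, the rates are 100/3520 = 2.8% vs 300/4480 = 6.7%, so an inert drug looks protective.

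**The case against.** Four points can be made for the plan.

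1. **The safety set may be in the analysis plan.** An exposure-based safety population is often left to a document not shown here, and its absence alone would be no defect. That is fair. But the protocol does more than stay silent: it fixes the grouping twice and says outcomes are compared between those groups, and adverse events are one of its outcomes.

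2. **This is the general grouping problem again.** The rule affects every outcome, recurrence included. That is true, but repairing the efficacy grouping would not by itself create a safety comparison. Nor would the planned propensity matching help, because balancing covariates cannot undo a classification made on what happened after treatment began.

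3. **Not every stop causes a switch.** Only intake below 80% of the planned amount does. For a 90-day course that is 0.80 × 90 = 72 days of full intake, so a patient who stops later can stay in the butylphthalide group. This stands and limits the size, and at 25% stopping the harm remains visible.

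4. **Adverse events are recorded in both groups.** A reader might infer from the outcome definition's reference to the trial group that other adverse reactions are collected in the butylphthalide arm alone, leaving nothing to compare. The documents do not support that. The definition does not say so. The abstract and the statistical methods refer to both groups, and Data management {19} puts adverse events on the case report form without restriction by group. Collection also cannot be confined to a group that is defined only after follow-up. One-arm collection would in any case remove the comparator or inflate the drug arm; it could not reverse the result. The phrase is a wording conflict to reconcile.

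**Conclusion.** The point holds for the grouping rule. As the protocol is written, patients whose butylphthalide intake falls below 80% because of harm count against routine care in the adverse-event comparison, and no stated step undoes this. The direction, towards no harm, follows from the rule together with event-driven stopping.

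The size is not known. Under the main illustration, a true excess of 5 points shrinks to 2.3 points at 25% stopping, almost vanishes at 50%, and reverses beyond about 54% of drug-caused events. All of these figures rest on assumed event rates, stopping shares and group sizes. It would be too strong to say that the comparison will reverse; what is established is that it is biased and can reverse.

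**What to change.** 1. For safety, define the groups by exposure: patients who took any butylphthalide versus patients who never took it. Keep stoppers and over-takers out of the unexposed comparator.
2. Report adverse events leading to discontinuation of butylphthalide separately.
3. In the Adverse events section, replace the reference to the trial group with a statement that adverse events are recorded the same way in both groups, in line with the abstract and Statistical methods {20a}.

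The cost is mainly wording and analysis. Medication is already to be recorded for all patients, including treatment periods, and the follow-up contacts at months 1, 3, 6 and 12 are already planned, so no extra patients or visits are needed. The safety groups will differ from the efficacy groups, which the report must explain, and the butylphthalide safety figures may look less favourable. The comparison remains non-randomised, so confounding by the choice to take butylphthalide still has to be addressed within the exposure groups.
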